#### Secondary objective(s)

2.5.2

To explore changes in the broader microbiome DNA landscape, including bacterial, viral, and archaeal DNA, in both fecal and blood samples before and after dairy consumption. This analysis aims to identify additional microbial signatures that may respond to dietary intervention and assess whether non-YDB microbial DNA in the blood mirrors corresponding shifts in the intestinal microbiome and yogurt consumption-induced effects on immune function.

#### Long-term objective

2.5.3

The ultimate objective is to develop technology capable of reliably characterizing the dynamics of microbiomes residing in and on the human body. This study will evaluate the extent to which this goal is achievable. It is anticipated that non-dairy-dependent microorganisms will exhibit relatively stable levels over time, whereas dairy-dependent organisms such as *Lactococcus* and *Bifidobacterium* species are expected to show measurable changes. Detecting will be critical for assessing the utility of blood microbiome technology in generating comprehensive, integrative descriptions of human-associated microbiomes.

### Power analysis

2.6

This is a pilot study. This research has never been conducted before, making it difficult to determine a definite sample size. Based on published studies showing significant change in the relative abundance of gut microbiome at the phylum level upon consumption of fermented milk in 6 volunteers (Firmicutes and Bacteroidetes; p < 0.05 when comparing milk consumption vs. baseline) [20], and that the relative abundance of Bifidobacterium species increased following the consumption of human milk oligosaccharides by 7 volunteers over 7 days (p < 0.05 when comparing four type of milk concentrations with baseline) [21], we have chosen to include 10 volunteers for this study. If this is not sufficient to convincingly demonstrate trends of *Lactococcus lactis* DNA during 7 days of milk consumption intervention, then blood microbiome studies may not be powerful enough to show meaningful changes in intestinal microbiome composition.

### Study procedures (Table 1)

2.7

#### Screening

2.7.1

Participants will undergo a medical history assessment and physical examination, including measurements of height, weight, blood pressure, and body mass index (BMI). Medical history will cover past and current diseases, medication use, and smoking status.

#### Baseline visit for milk withdrawal

2.7.2

Two weeks after the screening, participants will attend a morning baseline visit at the hospital. During this visit, medical history, body composition (weight, waist circumference, and BMI), and blood pressure will be assessed. Blood samples will be collected for blood microbiome analysis, and participants will be asked to provide a fecal sample (Table 2).From this day onward, participants will eliminate all dairy products from their diet for 10 consecutive days. Compliance with diary product withdrawal will be confirmed by direct interrogation at the sampling times, a questionnaire and by detecting YDB in the fecal samples using shotgun sequencing. Participants apparently not dairy-product withdrawn will be excluded from the final analysis and replaced by newly-recruited subjects.

**Table 1 tbl1:** Overview of study procedures.

	Study period (Days)					
	Enrollment	Milk withdrawal	Intervention			
Time	T = −15∗ day	T = −10 day	D_0_	D_1_	D_2_	D_7_
Suitability screening	X					
Informed consent	X					
Intervention: Milk withdraw → Yogurt reintroduction						
Measurements						
Anthropometric variables	X	X	X	X	X	X
Blood microbiome assessment		X	X	X	X	X
Fecal microbiome assessment		X	X	X	X	X
BMI		X	X	X	X	X
Blood pressure		X	X	X	X	X
Routine laboratory measurements		X	X	X	X	X

Note: D, Days; BMI, body mass index; ∗ will be differed depending on participant's availability.

**Table 2 tbl2:** Primary, secondary and exploratory outcomes.

Outcomes	Brief description	Time frame
Primary		
Blood MDB	Shotgun sequencing of whole blood DNA	−10, 0, 2, 3 and 7 days
Secondary		
Other blood microbes	Shotgun sequencing of whole blood DNA	−10, 0, 2, 3 and 7 days
The gut microbiome	Shotgun sequencing of fecal DNA	−10, 0, 2, 3 and 7 days
Exploratory		
BMI	Weight in kilograms and height in meters will be combined to report BMI in kg/m^2.	−10, 0, 2, 3 and 7 days
Blood pressure	Systolic and diastolic blood pressure will be assessed with a blood pressure monitor.	−10, 0, 2, 3 and 7 days

Note: MDB, milk-dependent intestinal bacteria.

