### Study design

2.1

We will perform a within-subjects crossover trial with a single arm to study the effect of yogurt on the blood and fecal YDB levels in healthy volunteers. Participants will first undergo a 10-day period of dairy product withdrawal. Given that the half-life of bacterial DNA in blood is likely less than 24 h, a 10-day withdrawal period should be sufficient to substantially reduce circulating DNA fragments originating from *L. lactis*. Following the reintroduction of dairy (via yogurt consumption that is host to LGG, LA-5 and BB-12 cultures), we expect these specific bacteria and other YDB DNA to reappear in the bloodstream. While the precise kinetics of this reappearance are not yet known, our study is designed to detect these temporal changes and establish a foundation for understanding the dynamic relationship between dietary intake, the gut microbiome, and the blood microbiome.

This study is approved by the ethics committee of Erasmus Medical University Center Rotterdam in May 2025 (NL88008.078.24) and is registered at www.clinicaltrials.gov (NCT06944002), hence prior to participant's enrollment. This study will be conducted in accordance with the principles of the Declaration of Helsinki (75th WMA General Assembly, Helsinki, Finland, October 2024) and the Medical Research Involving Human Subjects Act (WMO). Interested volunteers will be provided with detailed information about the study and will give written informed consent prior to participation.

Participants will be studied at multiple time points using a within-subject crossover design (Fig. 1). At baseline, prior to any dietary intervention, blood and stool samples will be collected. Following this, participants will abstain from all dairy products for 10 days, after which a second set of blood and stool samples will be collected to confirm the expected disappearance of YDB DNA from both fecal and circulating microbial DNA pools.

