**Fig. 2 fig2:**
[figure not shown]
Study schema. This study requires to include data from at least 10 participants.

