#### Primary objective

2.5.1

The primary objective is to examine yogurt-dependent bacterial (YDB) DNA counts in fecal and blood samples before and after dairy consumption. YDB, such as *Lactococcus lactis*, are transient residents of the human gut, only present following dairy intake, and therefore represent modifiable components of the intestinal microbiome. Detection of YDB DNA fragments in the bloodstream after dairy reintroduction will provide definitive evidence on the extent to which the blood microbiome reflects relevant changes in the intestinal microbiome. In this specific study, the use of a commercial yoghurt (but verified by independent agar growth testing) containing a defined consortium of bacteria adds signature species whose detection provides convincing signals in this respect.

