#### Pre-intervention visit

2.7.3

On the morning of day 11 (following the 10-day dairy withdrawal period), participants will return to the hospital and provide the same clinical data and biological samples to be collected during the baseline visit. For those who are unable to produce feces on the day of the scheduled visit, sample collection will be permitted either before or after the visit. To avoid confounding baseline measurements, yogurt consumption will only commence after the fecal sample has been collected. After sample collection, participants will begin reintroducing dairy by consuming yogurt for seven consecutive days. To reduce uncertainty regarding bacterial exposure, the number of viable bacteria will be quantified using MRS agar culturing, providing a trackable estimate of bacteria intake. These approaches will ensure microbial consistency across individual participants and minimize batch-related variability. As this is a pilot trial involving no more than 10 participants, it is not powered to assess dosage-dependent effects.

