### Statistical analysis

2.9

The primary outcome is the change in relative abundance of blood YDB DNA across five time points. This will be analyzed using repeated measures ANOVA to detect statistically significant within-subject changes over time. The secondary outcomes include changes in all other non-human microbial DNA, which will also be analyzed using repeated measures ANOVA. All statistical tests will be two-tailed, with significance set at p < 0.05.

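### The post-withdrawal stool YDB result can count towards excluding and replacing a participant, so the stool disappearance and rebound may partly reflect selection

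*Protocol article*

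**What the plan says.** Section 2.7.2 checks dairy withdrawal in three ways: direct questioning at the visits, "a questionnaire and by detecting YDB in the fecal samples using shotgun sequencing". The consequence follows at once: "Participants apparently not dairy-product withdrawn will be excluded from the final analysis and replaced by newly-recruited subjects". The sentence names no visit. Withdrawal runs from day −10 to D0, so the D0 stool is the natural sample to show whether it worked.

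The same stool measurement is a result elsewhere in the article:

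- Section 2.5.1: "The primary objective is to examine yogurt-dependent bacterial (YDB) DNA counts in fecal and blood samples before and after dairy consumption".
- Section 2.1 gives the purpose of the post-withdrawal samples: "to confirm the expected disappearance of YDB DNA from both fecal and circulating microbial DNA pools".
- Table 2 lists the gut microbiome, by shotgun sequencing of fecal DNA, as a secondary outcome.

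The formal primary outcome is in blood. Section 2.9 states: "The primary outcome is the change in relative abundance of blood YDB DNA across five time points". It is to be tested by repeated measures ANOVA, two-sided at 0.05.

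On numbers, the Fig. 2 legend says "This study requires to include data from at least 10 participants", while section 2.7.3 says "As this is a pilot trial involving no more than 10 participants".

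**The concern.** A person who truly abstains but whose stool stays positive (persistent carriage, another food source, a false-positive call) is evidence against the premise that YDB clears on withdrawal. The rule allows that person to be labelled non-withdrawn, removed and replaced by someone whose stool does clear. Keeping people with low stool YDB at D0 lowers the D0 mean. Values at the other visits are not selected, so they sit higher by regression to the mean. The result is a fall and a rebound even if diet does nothing.

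The decision probably also comes late. Yogurt starts once the D0 stool has been collected (section 2.7.3) and the next visit is 24 h later (section 2.7.4). Extraction, library preparation and sequencing are unlikely to be finished by then, so exclusion would probably be decided when post-yogurt samples already exist.

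The abstract says the study is to establish or rule out circulating microbial DNA as a representative of the gut microbiome. Removing people whose gut did not follow the expected pattern weakens the ruling-out half of that aim.

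**Working it through.** **The plan's own figure.** Section 2.6 chooses 10 volunteers by analogy with studies of 6 and 7. It gives no effect size, SD or power, so there is no calculation to reproduce.

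**Inputs from the article.** n = 10; five visits; repeated measures ANOVA; two-sided 0.05; exclusion and replacement tied to withdrawal status.

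**Assumptions, not in the article.** Stool YDB is normal on a log-type scale with SD 1. The within-person correlation (ICC) is 0.3 to 0.7. A share q with the highest D0 stool values is excluded and replaced. The stool–blood correlation ρ is 0 to 0.6. The true diet effect is zero. Here stool alone decides exclusion, so for a given q this is the strongest form of the filter.

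**Step 1: mean spurious rebound in stool.** Excluding the top share q at D0 moves the D0 mean to −φ(z)/(1 − q), where z is the (1 − q) quantile of the standard normal. An unselected visit moves by ICC times as much. Therefore

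rebound = (1 − ICC) × φ(z)/(1 − q).

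At ICC 0.5 and q = 0.3: z = 0.524, φ(z) = 0.348, and 0.5 × 0.348/0.7 = 0.25 SD. The fall from day −10 to D0 has the same size.

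**Step 2: false-positive rate of the stool ANOVA.** Simulation with 20,000 trials per setting, ICC 0.5:

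| Share excluded | Spurious rebound (SD) | Stool false-positive rate |
|---|---|---|
| 0% | 0.00 | 0.05 |
| 10% | 0.10 | 0.06 |
| 20% | 0.17 | 0.07 |
| 30% | 0.25 | 0.10 |
| 50% | 0.40 | 0.19 |

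The simulated rebounds agree with the Step 1 formula. At 30% excluded the rate runs from 0.08 (ICC 0.7) to 0.12 (ICC 0.3). At 50% it runs from 0.13 to 0.27.

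**Step 3: the blood outcome.** Blood is reached only through its correlation with stool, and its spurious rebound is ρ times that of stool. At ICC 0.5, 30% excluded and ρ = 0.6 this is 0.6 × 0.25 = 0.15 SD. The blood false-positive rates at 30% excluded are 0.05, 0.05 and 0.07 for ρ = 0, 0.3 and 0.6. At 50% excluded and ρ = 0.6 the rate is 0.09.

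**Step 4: an extreme case, for scale.** Suppose stool is scored detected or not, with the same probability p at every visit and independently between visits, and any D0 detection excludes. D0 detection is then zero by construction. A two-sided sign test of D0 against D7 needs at least 6 rises, since 2 × 0.5^6 = 0.031. Its false-positive rate is P(Bin(10, p) ≥ 6): 4.7% at p = 0.3, then 17%, 38%, 63% and 85% at p = 0.4, 0.5, 0.6 and 0.7. Retaining 10 people needs 10/(1 − p) completing withdrawal on average: about 17 at p = 0.4 and 33 at p = 0.7.

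**The case against.** Four points can fairly be made for the plan.

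1. Stool is one of three checks, and the text does not say that a positive stool alone leads to exclusion. A reader might infer that every stool-positive participant is dropped and that D0 stool is therefore negative by construction. The article does not support that. This point stands: the rule permits selection on the outcome but does not fix how much.
2. The formal primary outcome is blood YDB, which is not the filter. A reader might infer that the primary test is invalid. It is not; Step 3 shows almost no effect at 30% excluded. Nor is the blood–stool comparison settled in advance: blood may stay positive at D0 or fail to rise, and no post-yogurt sample is filtered. What remains is that participants in whom gut clearance failed can be missing from that comparison.
3. High exclusion shares look unlikely. The Introduction reports *L. lactis* undetectable in stool within four days of withdrawal, and withdrawal here lasts 10 days. A reader might take the 17% to 85% of Step 4 as the size of the problem. Those figures need a sign test instead of the planned ANOVA, detection independent between visits, and 40% to 70% of participants excluded. The ANOVA range is the one to use.
4. For a proof of concept, restricting to people with verified gut depletion is a reasonable per-protocol question about blood. That justifies a subset analysis, not making the restricted set the only one.

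The two statements about 10 participants are a minor wording matter. The upper limit can be read as 10 analysed, which replacement preserves.

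**Conclusion.** The concern holds in limited form. Section 2.7.2 lets a study outcome contribute to deciding who is analysed, and no other section of the article undoes this. To the extent that stool positivity drives exclusion, the stool disappearance and rebound are partly produced by selection, and blood is compared with stool in a sample chosen to fit the premise. The inflation is slight if few are excluded and material if a third or more are. The figures rest on the assumed normal scale, ICC and exclusion shares, and on stool deciding alone; if stool only supports self-report, the bias is smaller. This should be fixed before any sequencing result is opened, but it does not invalidate the primary blood test.

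**What to change.** - Exclude or replace no one because of the D0 stool YDB result.
- Make the main analysis all participants with a D0 sample and at least one post-yogurt sample.
- Report D0 stool YDB as an outcome, with the number still positive.
- Judge compliance from interview and questionnaire before sequencing results are opened, and use it only to define a per-protocol sensitivity analysis. Show the stool-negative subset as a second sensitivity analysis.
- Limit replacement to people who leave before D0, and reconcile the Fig. 2 legend with section 2.7.3 on the number of participants.

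With no exclusion on stool, the simulated false-positive rate returns to 0.048 to 0.050 and the spurious fall and rebound to 0.00 SD.

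The cost is a change of wording in the protocol and analysis plan. The downside is that a truly non-compliant participant stays in the main analysis. If that person shows no change, the mean change among 10 is diluted by 1/10, about a tenth; the per-protocol analysis shows whether this matters.

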#### Pre-intervention visit

2.7.3

On the morning of day 11 (following the 10-day dairy withdrawal period), participants will return to the hospital and provide the same clinical data and biological samples to be collected during the baseline visit. For those who are unable to produce feces on the day of the scheduled visit, sample collection will be permitted either before or after the visit. To avoid confounding baseline measurements, yogurt consumption will only commence after the fecal sample has been collected. After sample collection, participants will begin reintroducing dairy by consuming yogurt for seven consecutive days. To reduce uncertainty regarding bacterial exposure, the number of viable bacteria will be quantified using MRS agar culturing, providing a trackable estimate of bacteria intake. These approaches will ensure microbial consistency across individual participants and minimize batch-related variability. As this is a pilot trial involving no more than 10 participants, it is not powered to assess dosage-dependent effects.

#### Intervention visit

2.7.4

Participants will attend three additional morning visits during the intervention phase: Day 12 (24 h after reintroducing yogurt); Day 13 (48 h after reintroduction) and Day 18 (after 7 days of yogurt consumption). At each time point, participants will provide the same clinical and biological data as collected during the baseline visit. No follow-up visits are scheduled beyond this point.

### Milk dependent microbiome analysis pipeline

2.8

#### DNA extraction and shotgun sequencing

2.8.1

1Pipeline and experimental controls

As the central aim of this study is detect yogurt-derived bacterial DNA in blood, we will include an in-vitro control to validate the sensitivity and specificity of our detection pipeline. Blood sample collected at pre-intervention visit, following a 10-day withdrawal from yogurt and all other diary products, will be used for this purpose. Specifically, defined quantities of yogurt DNA will be spiked into participant blood samples prior to DNA extraction. This setup will allow us to confirm that our pipeline can reliably detect yogurt-derived bacterial DNA within a blood matrix (Fig. 3).

**Fig. 3 fig3:**
[figure not shown]
Pipeline designed to validate (circulating microbial DNA) cmDNA as a biomarker of the gut microbiota. A. In-vitro yogurt DNA spike-in control. To assess whether intestinal bacterial DNA enters the circulation and is detectable in the blood, DNA extracted from three commercial yogurt samples of the same batch will be pooled based on concentration, serially diluted, and spiked into participant blood samples (e.g., from the pre-intervention visit) prior to DNA extraction. These spiked samples, together with non-spiked baseline blood DNA sample and pooled yogurt DNA, will undergo shotgun sequencing and taxonomic profiling. This provides both quantitative and qualitative benchmarks for detection sensitivity and specificity. B. Reference controls without the spike in. To explore the existence of a core blood microbiome and distinguish the true microbial signals from background noise, the study includes serval refence controls, which will be processed without added microbial DNA or any artificial spike-in, maintaining its original state to serve as benchmark background signal and classification fidelity: (i) placenta blood as negative control; (ii) blood from patients infected with known viruses as a positive control (blood will be obtained from the Erasmus MC virology department); (iii) human-deprived organoids to assess database classification accuracy and text whether human genomic sequences are misclassified as bacterial in tools like Kraken 2; (iv) whole blood from healthy pigs as a translational non-human host control, based on the hypothesis that pigs may harbor a core cmDNA signature due to dietary and physiological similarities with human. This also reflects the growing relevance of pigs as organ donors in translational research; and (v) rat blood as a preclinical non-human host control, representing a widely used model in experimental and pharmacological studies.

To further evaluate the sensitivity and specificity of the entire blood microbiome analysis pipeline, from DNA extraction to data interpretation, a defined microbiome standard (e.g., ZymoBIOMICS Microbial Community DNA Standard) will be included. This benchmark will enable assessment of extraction efficiency, sequencing accuracy and taxonomic profiling cross the pipeline.

Because the blood microbiome may be less than 5 % of the entire blood DNA, interpretation of such low microbial biomass is challenged by potential environment contamination (e.g., lab equipment and kitome) [22,23]. In addition, the definition of a core blood microbiome is further complicated by that the assembled genomes of many bacteria (especially older assemblies) are contaminated by human DNA sequences, leading to false-positive results. The latter issue is considered the biggest problem in the analysis and interpretation of blood microbiomes [14]. The current study, because of its longitudinal character and its reliance on the introduction of defined species with relatively novel assemblies in the database, is designed to provide of proof-of-principle on whether these problems can be overcome. Further, additional power will be added to the current study by introduction of additional controls: we will include a series of reference controls designed to account for all potential sources of contamination and misinterpretation described above (Fig. 3).2DNA extraction and shotgun sequencing

To minimize the cross-contamination of kitome from different DNA isolation kits, we will choose the same kits from same company to isolate DNA from all samples types, including feces and blood. The analysis of the cmDNA may follow a slightly modified version of our previously published pipeline [24]. Briefly, fasting blood (5 mL) will be collected by a certified phlebotomist at each time point. Of this, 2.5 ml will be used for DNA extraction and remainder for plasma collection. The samples will be stored at −80 °C until further processing. The blood YDB and other microbial DNA will be assessed by sequencing following the steps below: 1) Blood DNA will be extracted by a commercial available kit or a modified cetyltrimethylammonium bromide (CTAB) method [25]. Briefly, 1000 μl of CTAB lysis buffer at 65 °C with lysozyme will be added to 250 μl of the whole blood and gently inverted. After centrifugation at 12 000 rpm for 10 min, the supernatant will be transferred into a 2.0 ml tube containing phenol/chloroform/isoamyl alcohol (25:24:1). Following another centrifugation, the supernatant will be moved into a new tube, mixed with 24:1 isoamyl alcohol and centrifugated again. The supernatant will be mixed with isopropanol, incubated at −20 °C, and discarded. The precipitate will be washed with 1000 μl of 75 % ethanol twice, dried and dissolved in dd H_2_O. Finally, 1 μl of RNase A will be added, and the mixture will be incubated at 37 °C for 15 min; 2) DNA degradation will be monitored on 1 % agarose gels, and concentration will be measured using Qubit® dsDNA Assay Kit in Qubit® 2.0 Flurometer (Life Technologies, CA, USA). Samples with an OD value between 1.8 and 2.0 and contents above 1ug will be used for library construction; 3) Sequencing libraries will be created using NEBNext® Ultra DNA Library Prep Kit for Illumina (NEB, USA). First, index codes will be added to sequences. Then, DNA sample will be fragmented into approximately 350 bp by sonication, then end-polished, A-tailed, and ligated with adaptors for Illumina sequencing via PCR. Lastly, PCR products with universal primers will be purified (AMPure XP system), with libraries analyzed for size distribution by Agilent2100 Bioanalyzer and quantified using real-time PCR; and 4) The clustering of index-coded samples will be performed on a cBot Cluster system. After cluster generation, DNA library will be sequenced on an Illumina PE150 platform, generating paired-end reads.

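### The control set is said to cover every contamination source described, but no listed control is reagent-only, and a DNA standard cannot test the cell-lysis part of extraction efficiency.

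*Protocol article*

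**What the plan says.** Section 2.8.1 describes two threats to reading microbial DNA in blood. One is laboratory contamination, with the examples "e.g., lab equipment and kitome". The other is human sequence sitting inside bacterial reference assemblies, which the article regards as the larger problem. It then claims full coverage of both: "we will include a series of reference controls designed to account for all potential sources of contamination and misinterpretation described above".

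The Fig. 3 legend lists the unspiked controls: "i) placenta blood as negative control", blood from patients with known viral infections, "human-deprived organoids to assess database classification accuracy", pig blood, and "rat blood as a preclinical non-human host control". The spike-in arm consists of participant blood with added yogurt DNA, the same blood without it, and the pooled yogurt DNA. A microbial community DNA standard is given as an example benchmark, and the text says of it: "This benchmark will enable assessment of extraction efficiency, sequencing accuracy and taxonomic profiling cross the pipeline".

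The same section promises one supplier's kits for all sample types, but leaves blood extraction open between a commercial kit and a CTAB method. It sets an entry rule for sequencing based on an OD range and DNA content: "contents above 1ug will be used for library construction". Section 2.8.4 applies the blood extraction method to faeces. Section 2.9 makes the relative abundance of blood YDB DNA over five time points the primary outcome.

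**The concern.** The study sets out to settle whether microbial DNA in blood is real, in a field where contamination is a main objection. The article itself says that "interpretation of such low microbial biomass is challenged by potential environment contamination (e.g., lab equipment and kitome") is a difficulty. A control isolates reagent background only if nothing else in the tube can supply microbial reads. None of the listed controls meets that condition.

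The laboratory also handles the target organisms: yogurt DNA is pooled, diluted and spiked (Fig. 3), and yogurt is cultured (Section 2.7.3). Carry-over would produce reads of exactly the species that the primary outcome counts.

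The extraction benchmark has a separate gap. Purified DNA skips the step in which cells are opened, so it cannot report how well that step works. Section 2.7.2 uses faecal YDB sequencing as one of three checks of dairy withdrawal, and apparent non-compliance leads to exclusion and replacement. Poor lysis in faeces would therefore affect more than a descriptive result.

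**Working it through.** The plan has no figure of its own on this point. The check sets the claimed coverage against the list, then uses assumed values to show the direction of effect.

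**1. Controls against sources**

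| Listed control | What it can show | Reagent-only? |
|---|---|---|
| Blood spiked with yogurt DNA before extraction | recovery and detection of free DNA | no |
| Unspiked pre-intervention blood | the participant's own level | no |
| Pooled yogurt DNA | taxa the yogurt yields | no |
| Placenta blood | background in a human matrix | no |
| Virus-infected patient blood | detection of a known agent | no |
| Organoids | human sequence misread as bacterial | no |
| Pig blood | non-human host; the article expects it may hold a core signature | no |
| Rat blood | non-human host | no |
| Community DNA standard | purification, sequencing, classification | no |

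The count is 0 of 9. Write the microbial reads in an unspiked control as K + C + H + T, where K is kit or reagent DNA, C carry-over, H misclassified host sequence and T true microbial DNA. Each biological control gives one total with H, T or both unknown. A reagent-only blank has H = T = 0 and reads K + C directly.

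**2. Effect on the primary outcome**

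Assume that relative abundance is taken over non-host reads: R = Y / (Y + M + K), with Y the YDB DNA and M other microbial DNA. The values are illustrative: Y = 1, M = 9.

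| K | R |
|---|---|
| 0 | 1/10 = 0.100 |
| 2 | 1/12 = 0.083 |
| 10 | 1/20 = 0.050 |
| 40 | 1/50 = 0.020 |

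- *Constant K.* If Y goes from 0 to 1, R goes from 0 to 0.100 with K = 0, and from 0 to 0.050 with K = 10. The change is diluted, but none is created.
- *Varying K.* If Y stays at 1 while K goes from 2 in one batch to 10 in another, R falls from 0.083 to 0.050, a 40% drop (1 − 12/20) with no biological change. If batches line up with visits, this looks like a time effect.
- *Carry-over.* C of a yogurt species adds to the numerator, so it can create an apparent rise even when Y = 0.

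**3. What a DNA standard reads**

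Let recovery be the lysis yield times the purification yield, with purification assumed to be 0.70. A DNA standard bypasses lysis and reads 0.70 whatever the lysis yield.

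| Lysis yield | DNA standard | Intact cells |
|---|---|---|
| 0.2 | 0.70 | 0.14 |
| 0.5 | 0.70 | 0.35 |
| 0.8 | 0.70 | 0.56 |
| 1.0 | 0.70 | 0.70 |

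The Introduction defines the blood target as DNA fragments and not living cells, so for blood the 0.70 is the relevant quantity. For bacteria that reach faeces as cells it is not.

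**4. How many blanks help**

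If a contaminant shows in one blank with probability p, the chance of seeing it in at least one of n independent blanks is 1 − (1 − p)^n.

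| p (assumed) | n = 1 | n = 3 | n = 5 | n = 10 |
|---|---|---|---|---|
| 0.1 | 0.10 | 0.27 | 0.41 | 0.65 |
| 0.3 | 0.30 | 0.66 | 0.83 | 0.97 |
| 0.5 | 0.50 | 0.88 | 0.97 | 0.999 |

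One blank for the whole study would be weak. One per batch accumulates.

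**The case against.** The strongest reply is that the design already carries most of the load. Each participant is sampled at baseline, after withdrawal and three times after reintroduction, and Section 2.8.1 relies on this and on defined species. A steady kit background cannot make LGG, LA-5 and BB-12 vanish and return. That stands. It does not cover background that differs between lots or batches, or carry-over.

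Second, the biological controls should pass through the same kits, so taxa common to all of them do say something about background. That also stands, but the view is partial and confounded. The organoid control answers the human-sequence problem, which is a different source.

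Third, defined amounts of yogurt DNA go into blood before extraction, so free-DNA recovery is measured in the right matrix. That stands in full for the primary outcome.

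Fourth, this is a condensed article: blanks may appear in a fuller protocol or in the cited pipeline, the Fig. 3 image was not available, and the standard is only an example. This would be decisive if the article were merely silent. Here it itemises its controls and claims completeness for them.

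Fifth, the OD and DNA-content rule is worded for samples and does not say how controls are treated. That it would shut out a blank is an inference, which is why the fix asks for a statement.

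**Conclusion.** The coverage statement is not supported by the listed controls: 0 of 9 isolates kit and reagent DNA or yogurt-DNA carry-over. The extraction-efficiency statement is not supported for cell lysis if the example DNA standard is used. Both gaps should be closed before samples are extracted; neither invalidates the design.

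A reader might infer more than this. The documents do not support the reading that kit DNA and extraction loss can never be told from signal: the within-subject sequence, the shared kits and the pre-extraction spike each supply information. Nor do they support a figure for background as a share of the YDB signal, because no read counts are given. No step that subtracts placenta-blood taxa is described, so loss of true signal by that route cannot be charged to the plan.

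The remaining exposure is conditional. It requires background that varies between lots or batches, or carry-over, together with a denominator of non-host reads for the dilution effect. The article does not say how samples are batched. The values in the working are assumptions that show direction, not estimates.

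**What to change.** 1. Include at least one extraction blank and one no-template library control in every extraction and library batch.
2. State that these are sequenced regardless of the OD and DNA-content criteria in Section 2.8.1.
3. Use them together with the biological controls to judge background for each YDB species. A blank contains no host DNA, so its percentages are not directly comparable with those from blood.
4. Process each participant's five visits in the same batch, so that batch differences cannot pass for time effects.
5. Use a whole-cell community standard for extraction efficiency, and keep the DNA standard for sequencing and classification.

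If these are not adopted, narrow the text: say that the controls address misclassification and give an indirect view of laboratory background, and limit the extraction claim to recovery of free DNA.

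The cost is a few extra libraries per batch and a different standard for one purpose. Participants are not affected.
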